### Participants

This pilot will enroll licensed primary care clinicians, including physicians, nurse practitioners, and physician assistants. Inclusion criteria require health care providers to have ≥0.5 full-time equivalent dedicated to adult diabetes care at participating sites, the ability to complete 2 simulation periods, and provision of informed consent. Exclusion criteria include prior participation in any FibroX usability or validation studies, exclusive practice in pediatrics or nondiabetes specialty areas, or inability to complete all study procedures. Participating clinicians are expected to have varying levels of clinical experience, reflecting real-world primary care practice, but all are required to have active involvement in the management of adult patients with T2D to ensure familiarity with relevant clinical workflows and decision-making. Participants will be recruited through email invitations and departmental announcements across Yale-affiliated primary care and diabetes clinics, as well as participating federally qualified health centers. Recruitment will target clinicians with active involvement in the management of adults with T2D, with participation on a voluntary basis.

The simulation case library will comprise adult patients (aged ≥18 years) with T2D and at least one additional MASLD risk factor (eg, obesity, dyslipidemia, and hypertension). Each case must have a ground-truth fibrosis stage determined by liver biopsy or expert consensus based on VCTE. To ensure fidelity to real-world clinical presentation, cases will include complete routine clinical data such as age, AST, ALT, platelet count, HbA_1c_, BMI, and creatinine or estimated glomerular filtration rate, along with relevant clinical notes. The simulation case library will be developed using deidentified or synthetic cases derived from representative clinical datasets and prior cohorts, with case selection designed to capture a range of fibrosis risk profiles and clinical presentations. Cases will be curated to ensure clinical realism, balanced representation across fibrosis stages, and inclusion of all variables required for FibroX and comparator assessments.

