### Interventions

The intervention arm, known as FibroX-enabled care, will use a simulated EHR-like interface delivered through a secure web-based platform that mirrors the presentation of routine outpatient clinical information. Participants will review standardized simulated cases containing patient demographics, relevant clinical history, laboratory data, and clinical notes. Within this interface, FibroX-enabled care will display key predictive and explanatory information at the point of decision-making. This will include individualized FibroX risk estimates for advanced fibrosis generated using routinely available clinical data. Crucially, the interface presents dual-threshold triage bands aligned with established clinical guidance, classifying patients into 3 actionable categories: rule out, indeterminate (with a pathway to VCTE or other noninvasive testing), and rule in (with a pathway to hepatology referral). In addition, the interface presents case-level SHAP outputs that display the relative contribution of individual clinical variables (eg, age, AST, ALT, platelet count, HbA_1c_, BMI, and kidney function) to the predicted risk of advanced fibrosis. These explanations are presented in a structured visual format, such as ranked feature contributions, alongside the risk estimate and triage category to support clinician interpretation at the point of decision-making. By providing case-level explanations of the key drivers of predicted risk, these SHAP-based outputs are intended to support clinician interpretation of the model’s recommendations, increase confidence in triage decisions, and facilitate more consistent application of guideline-concordant referral pathways compared with usual care, where risk estimation is often implicit and variable.

The comparator arm, designated as usual care, will present the same standardized clinical case information within the simulated EHR-like interface but without FibroX risk estimates, SHAP explanations, or AI-based triage support. Participants in this arm will make diagnostic and management decisions based on routine clinical judgment alone. Optional access to a basic FIB-4 calculator will be provided, reflecting common clinical practice for noninvasive fibrosis risk stratification. FIB-4 is a widely used blood-based fibrosis score derived from age, AST, ALT, and platelet count to estimate the likelihood of advanced fibrosis [23].

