### Outcomes

The primary end points of this pilot study are the feasibility and usability of FibroX-enabled care within diabetes-focused clinical workflows. Feasibility will be assessed using recruitment and study completion rates, with prespecified targets of enrolling at least 70% of eligible clinicians and achieving a completion rate of at least 85% among enrolled participants. Completion will be defined as participants completing both simulation periods, including all assigned cases and postperiod surveys. Participants who do not complete both periods or required assessments will be classified as incomplete. Usability will be evaluated using the System Usability Scale (SUS), with a prespecified success threshold of 70 or higher.

Secondary end points include workflow efficiency and preliminary diagnostic performance. Workflow efficiency will be assessed by median time per case, with an anticipated threshold of 3.5 minutes or less. Preliminary diagnostic performance outcomes will include sensitivity, specificity, and the area under the receiver operating characteristic curve for the detection of MASLD-associated advanced fibrosis. Calibration will be examined using intercept, slope, and graphical assessment of predicted versus observed risk.

Exploratory end points will include clinician trust and cognitive workload, assessed using the AI trust scale and National Aeronautics and Space Administration Task Load Index (NASA-TLX), respectively, as well as implementation-related outcomes, including the proportion of guideline-concordant referrals and net reclassification improvement. Qualitative debrief interviews will further explore clinician understanding, interpretability, and perceived usefulness of the SHAP-based explanations, including how these outputs influence decision-making and trust in the model. These measures are intended to provide pilot estimates and inform the design, end point selection, and sample size considerations for a future definitive trial.

At a high level, this pilot will be considered successful if predefined feasibility and usability thresholds are met, including adequate recruitment and completion rates and a SUS score of 70 or higher, alongside signals of acceptable workflow efficiency and improved or comparable diagnostic performance relative to usual care. These criteria are intended to determine whether progression to a larger, real-world trial is justified.

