### Data Collection Methods

The platform automatically logs case navigation, decisions, timestamps, and use of FibroX features and overrides. Clinicians will not receive case-level performance feedback during either simulation period. Feedback, if provided, will be deferred until completion of the study period to minimize within-period learning effects. Surveys (SUS, AI trust, and NASA‑TLX) are administered electronically at the end of each period. Qualitative debriefs are audio-recorded and transcribed for thematic analysis. Completeness checks and range validations occur at ingestion.

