### Statistical Analysis

All analyses will follow an intention-to-treat principle, including all health care provider decisions regardless of sequence assignment. The primary comparison of diagnostic accuracy between FibroX-enabled care and usual care will use paired analyses to account for the crossover design. Sensitivity and specificity for detecting MASLD-associated advanced fibrosis will be compared using McNemar test for paired proportions. Overall discrimination will be assessed by calculating the area under the receiver operating characteristic curve for each condition, and calibration will be evaluated through intercept, slope, and calibration plots to determine agreement between predicted probabilities and observed outcomes.

To account for clustering at the health care provider level and the crossover design, mixed-effects logistic regression models will be used, specifying health care provider as a random effect and study condition, study period, and sequence assignment as fixed effects. Sensitivity analyses will also assess whether diagnostic performance differs by sequence assignment or period, which may suggest residual carryover or learning effects. These models will also adjust for case-level covariates such as age, BMI, and HbA_1c_ to explore potential confounding and heterogeneity. Secondary analyses will include net reclassification improvement to quantify whether FibroX improves assignment of cases into clinically appropriate triage categories compared with usual care. Bootstrap resampling will be used to generate CIs for net reclassification improvement and calibration metrics, ensuring robust estimation under small-sample conditions.

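### AUROC is planned for each condition without a graded clinician rating common to both, and the FibroX calibration intercept in a stage-balanced library can reflect case selection

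*Protocol article*

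**What the plan says.** **Discrimination.** Under Statistical Analysis: "Overall discrimination will be assessed by calculating the area under the receiver operating characteristic curve for each condition". The Outcomes section lists AUROC, with sensitivity and specificity, as a secondary end point.

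**Calibration.** Under Outcomes: "Calibration will be examined using intercept, slope, and graphical assessment of predicted versus observed risk". Under Statistical Analysis: "calibration will be evaluated through intercept, slope, and calibration plots to determine agreement between predicted probabilities and observed outcomes". Neither sentence names the condition.

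**What usual care produces.** The Interventions section shows the usual-care case "but without FibroX risk estimates, SHAP explanations, or AI-based triage support", and adds: "Participants in this arm will make diagnostic and management decisions based on routine clinical judgment alone". A FIB-4 calculator is available but optional. The same section contrasts FibroX-enabled care with usual care in these words: "compared with usual care, where risk estimation is often implicit and variable".

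**What is recorded.** Under Data Collection Methods: "The platform automatically logs case navigation, decisions, timestamps, and use of FibroX features and overrides". Table 1 also schedules a confidence item in both periods, without a scale and without a link to the AUROC.

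**Case mix.** The Participants section asks for "balanced representation across fibrosis stages" in the case library. The Introduction says that FibroX was derived on population-based survey data. The article mentions no reweighting of cases to a target prevalence.

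**The concern.** An AUROC needs a score that orders cases. In FibroX-enabled care two kinds of score are possible: the tool's continuous risk, or something the clinician enters after seeing it. In usual care only the second kind exists for every case, since FIB-4 is optional. The plan does not say which score it means.

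The choice matters because a continuous score and a coarse decision give different AUROCs for the same underlying ability. Scoring the algorithm's risk against clinicians' decisions would answer whether the algorithm beats clinicians. The trial asks whether clinicians decide better with the tool than without it. The Outcomes section includes diagnostic performance relative to usual care among the signals for moving to a larger trial, so a scoring artefact could enter that judgement.

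Calibration raises a separate problem. An intercept compares mean predicted risk with the observed proportion. If cases are selected by stage, the design sets the observed proportion, and a departure from zero need not say anything about the model.

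**Working it through.** **The plan's own figure.** No figure is given for AUROC or calibration. The one nearby figure is the decision count: 36 × 32 = 1152 and 40 × 32 = 1280, which matches the stated 1150 to 1280. It does not bear on this point.

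**1. AUROC from scores of different coarseness**

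Assumptions: equal-variance binormal ratings and a true AUROC of 0.80 in both conditions. Neither is in the protocol.

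- Separation: d = √2 × z(0.80) = 1.414 × 0.842 = 1.19.
- Yes/no decision at the best cut: AUROC = Φ(d/2) = Φ(0.595) = 0.724.
- Yes/no decision at specificity 0.90: sensitivity = Φ(1.19 − 1.28) = 0.464; AUROC = (0.464 + 0.90)/2 = 0.682.
- Three categories, cuts at specificity 0.90 and 0.50: sensitivities 0.464 and Φ(1.19) = 0.883. Trapezoids: 0.10 × 0.464/2 + 0.40 × (0.464 + 0.883)/2 + 0.50 × (0.883 + 1)/2 = 0.023 + 0.269 + 0.471 = 0.763.

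A separate simulation with d = 1.2 and other cuts gave 0.802 (continuous), 0.768 (three categories) and 0.726 (yes/no).

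| Usual-care score | AUROC | Apparent deficit against the continuous score |
|---|---|---|
| Three categories | 0.763 to 0.768 | 0.03 to 0.04 |
| Yes/no, best cut | 0.724 to 0.726 | 0.08 |
| Yes/no, specificity 0.90 | 0.682 | 0.12 |

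The whole deficit comes from scoring. It vanishes if both conditions use the same rating scale.

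**2. Calibration intercept under selection by stage**

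For a model perfectly calibrated in its source population, changing only the share of F3 or higher shifts the intercept by

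logit(library prevalence) − logit(source prevalence).

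The protocol states neither prevalence. Assume 40% in the library if F0 to F4 are equally represented (2 of 5 stages), or 50% if cases at F3 or higher and cases below F3 are equal in number.

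| Source prevalence (assumed) | Library 40% | Library 50% |
|---|---|---|
| 5% | +2.54 | +2.94 |
| 10% | −0.41 + 2.20 = +1.79 | +2.20 |
| 20% | −0.41 + 1.39 = +0.98 | +1.39 |
| 40% | 0 | +0.41 |

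A simulation (linear-predictor SD 1.5, assumed) agrees. With source 10% and library 40%, mean predicted risk is 0.16 against 0.40 observed, the intercept is +1.79 and the slope 0.99. The slope stays near 1 when only the share of F3 or higher changes.

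Equalising all five stages also changes the mix within each class. With an assumed source split of 60/25/15% for F0/F1/F2 and 60/40% for F3/F4, and source prevalences of 20% down to 5%, the slope falls to 0.81 to 0.84 and the intercept is +0.8 to +2.3. AUROC falls from 0.82 to 0.84 in the source to 0.77 to 0.79 in the library.

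**The case against.** The other side has several good points.

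- **A reader might infer that usual-care AUROC cannot be computed because no probabilities exist.** That does not follow. AUROC needs only an ordinal rating. Confidence is scheduled in both periods, and the planned net reclassification analysis implies triage categories in both conditions. The gap is that no common rating is named.
- **A reader might infer that the plan promises usual-care calibration it cannot deliver.** The phrase about each condition attaches to AUROC alone, and the calibration sentences can be read as FibroX only.
- **A reader might infer that the comparison will favour FibroX.** The article never says that the tool's score stands in for the clinician's decision. The bias is conditional on using different scales.
- **A reader might infer that FibroX calibration is wrong by construction.** The shift is zero at equal prevalences, the slope is untouched by a pure change in the share of F3 or higher, and balanced representation need not mean equal stages.
- **A reader might infer that calibration intervals will be several times too narrow because many clinicians read each case.** The article gives neither the case assignment nor the bootstrap unit, so no such factor can be derived.

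It is also fair that a condensed article may leave the rating field to the full protocol, and that the logging sentence is not exhaustive, since it omits the confidence item. If a common rating is already defined there, the first part reduces to a sentence of clarification. It is still worth raising now, because a rating not collected during the simulation cannot be recovered by a later analysis plan. The conflict over case mix lies between two choices that the article does state.

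Finally, a compulsory probability could make an implicit judgement explicit in the comparator, and clinicians could copy the displayed FibroX risk. Both points stand and bear on which rating to choose.

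**Conclusion.** The concern holds in two limited parts.

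First, the score behind the AUROC is undefined, and the article ties no graded clinician rating to it in both conditions. If FibroX's continuous risk were set against usual-care decisions, coarse scoring alone would favour FibroX by about 0.03 to 0.12, depending on the cut. This rests on the binormal model and an assumed true AUROC of 0.80 in both.

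Second, the FibroX calibration intercept reflects case selection whenever the library prevalence differs from the prevalence the model is calibrated to. For an assumed 40% in the library and 10% to 20% in the source, a perfect model shows about +1.8 to +1.0.

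This should be fixed, but it is not critical. The primary end points are feasibility and usability, and the sensitivity and specificity comparisons, which rest on decisions, are unaffected by how the AUROC is scored.

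**What to change.** 1. Before the platform is locked, specify one graded clinician rating of F3 or higher per case, collected identically in both conditions. A defined decision-plus-confidence scale, the clinician's triage category or a probability would each serve. Compute both AUROCs from it.
2. Report FibroX stand-alone discrimination and calibration separately, under that label, with distinct cases as the resampling unit.
3. State that calibration concerns FibroX only. Either reweight it to a stated target prevalence, using the known stage-sampling fractions (weight = target share of the stage divided by its library share), or drop the intercept.

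**Cost.** Using the existing confidence item costs almost nothing beyond defining its scale. A new field adds a few seconds per case, equally in both conditions, with a small effect on time per case (which has a 3.5-minute threshold) and on workload. The rest is a few sentences of analysis text. The article reports that platform finalization and case library validation were still under way at submission, so the change is cheap now.

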### Sample Size

At least 36 health care providers (32 cases/health care provider) yield 1150 to 1280 paired decisions. Under pilot assumptions (accuracy 0.60 usual care vs 0.75 FibroX), McNemar test provides >80% power to detect a 15-point improvement at α=.05 after accounting for health care provider–level clustering via a conservative design effect. Precision estimates for feasibility and usability metrics are expected to be narrow enough to inform a subsequent multicenter trial.

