### Randomization, Allocation Concealment, and Implementation

Health care providers will be randomized 1:1 to AB (FibroX then usual care) or BA (usual care then FibroX) using a computer-generated schedule prepared by a statistician not involved in recruitment (Figure 2). Allocation will be concealed via a secure, centralized randomization module until assignment. The research coordinator enrolls participants and implements sequence assignments.

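### The mixed model names provider as its only random effect, so the CI for the FibroX effect is too narrow if clinicians differ in how much they gain from the tool

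*Protocol article*

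**What the plan says.** Clinicians are the randomised unit: "Health care providers will be randomized 1:1 to AB (FibroX then usual care) or BA (usual care then FibroX"). Under Trial Design and Oversight, each clinician works through a different set of cases in each period, so the data form two blocks of decisions per clinician, one per condition.

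The Statistical Analysis section gives the purpose of the model: "To account for clustering at the health care provider level and the crossover design, mixed-effects logistic regression models will be used". It then fixes the structure: "specifying health care provider as a random effect and study condition, study period, and sequence assignment as fixed effects". Case-level covariates are added as adjustments. No random slope, provider-by-period effect, cluster-robust standard error or clinician-level resampling is named for the condition effect.

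The Sample Size section says "At least 36 health care providers (32 cases/health care provider) yield 1150 to 1280 paired decisions". It assumes "accuracy 0.60 usual care vs 0.75 FibroX" and states that "McNemar test provides >80% power to detect a 15-point improvement at α=.05" "after accounting for health care provider–level clustering via a conservative design effect". It gives no value for the design effect or the ICC.

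**The concern.** A clinician intercept common to both blocks largely cancels from the within-clinician comparison of FibroX with usual care. What stays in that comparison, besides binomial noise, is any difference between clinicians in their gain from FibroX or in their shift between periods. The stated model has no term for this. Given the intercept, it treats all decisions as independent, and its standard error for the condition effect reflects binomial noise only.

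Nothing else named in the article fills the gap:

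- The McNemar test has no clinician term.
- The bootstrap is confined to net reclassification improvement and calibration.
- The sequence, period and carryover checks are fixed effects.
- The design effect belongs to the sample size, not the analysis.

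The mixed model is therefore the only named accuracy analysis meant to handle clustering.

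Variation in gain is plausible here. The trial enrols physicians, nurse practitioners and physician assistants with differing experience, measures trust in the tool, and records how it is used: "The platform automatically logs case navigation, decisions, timestamps, and use of FibroX features and overrides". At stake are the interval and p value for the FibroX effect. They may colour the judgement of whether diagnostic performance is improved or comparable, which is part of the pilot's overall success criterion. The pilot is also meant to inform the sample size of a later trial, and an intercept-only model never estimates the between-clinician effect variance that this needs.

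**Working it through.** **The plan's own figures.** 36 × 32 = 1152 decisions; 1280 corresponds to 40 × 32 (40 clinicians is an inference). For McNemar power, take d = 0.15 and, for independent responses, a discordant proportion ψ = 0.60 × 0.25 + 0.40 × 0.75 = 0.45. The required number of pairs is n = (1.96√ψ + 0.8416√(ψ − d²))² / d² = (1.96√0.45 + 0.8416√0.4275)² / 0.0225 ≈ 155. Power above 80% therefore holds for any design effect up to 1152/154.6 = 7.45 (ICC about 0.21 with 32 per cluster), or 576/154.6 = 3.73 (ICC about 0.18 with 16 per cluster). The power statement holds as a bound. The concern is with the analysis model.

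**Inputs.** From the article: 36 clinicians, 1:1 allocation (taken as 18 and 18), two-sided α of .05. The 32 cases per clinician may be a total (16 per condition) or a per-period figure (32 per condition), so both were run. Assumed, because the article gives no value: ICC within clinician and condition of 0.05 to 0.10, with a share c of 0.8 or 0.5 common to both conditions.

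**Closed form.** True variance of the condition contrast divided by the variance the stated model assumes, with m decisions per condition:

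R = [1 + (m − 1)·ICC − m·c·ICC] / [1 − c·ICC]; false-positive rate = 2[1 − Φ(1.96/√R)].

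Example, m = 16, ICC 0.05, c = 0.5: (1 + 0.75 − 0.40)/0.975 = 1.385; √R = 1.177; 1.96/1.177 = 1.666; rate 9.6%. With c = 1, R = 1 and the rate is 5%.

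**Simulation.** The stated model was fitted by maximum likelihood to trials with no FibroX effect and accuracy 0.60 in both conditions, 1000 to 1500 trials per setting:

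| m per condition | ICC | c | R | Closed form | Simulated |
|---|---|---|---|---|---|
| 16 | 0.05 | 0.8 | 1.16 | 6.8% | 7.1% |
| 16 | 0.05 | 0.5 | 1.38 | 9.6% | 9.9% |
| 16 | 0.10 | 0.8 | 1.33 | 8.9% | 10.1% |
| 16 | 0.10 | 0.5 | 1.79 | 14.3% | 14.4% |
| 32 | 0.05 | 0.8 | 1.32 | 8.8% | 8.5% |
| 32 | 0.05 | 0.5 | 1.79 | 14.3% | 13.6% |
| 32 | 0.10 | 0.5 | 2.63 | 22.7% | 19.7% |

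In the last row the closed form runs above the simulation, so the simulated value is used. With the correlation fully shared, the simulated rate was 4.0% to 4.5%. A t test on per-clinician period differences gave 5% to 7% in every setting.

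**Second parametrisation.** Let the FibroX log-odds ratio vary between clinicians with SD τ (assumed; intercept SD 0.5 and mean accuracy 0.675 also assumed), 500 null trials per setting:

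| τ | 0 | 0.25 | 0.5 | 0.75 |
|---|---|---|---|---|
| Stated model, 16 per condition | 4.8% | 5.2% | 10.8% | 13.4% |
| Stated model, 32 per condition | 5.6% | 7.8% | 14.2% | 24.0% |

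The per-clinician t test stayed between 4.2% and 6.0%.

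**The remedy itself.** A provider-by-condition random effect with 34 degrees of freedom was fitted in 600 null trials at 16 per condition, ICC 0.05, half shared. It gave 6.0%, against 9.3% for the stated model and 6.2% for the per-clinician t test. With the correlation fully shared it gave 4.5%, against 5.3% for the stated model.

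**The case against.** The strongest reply is that a condensed article need not spell out a covariance structure. The text does not literally say intercept only, and an unseen analysis plan could add a slope. That is fair as far as it goes. But the article does specify a model rather than leave it open, gives clustering and the crossover as the reason for it, and names a single random effect. The ordinary reading is an intercept.

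Second, the narrowing depends on a variance that the article does not give. This stands. With no clinician-by-condition variation the model keeps its level, and at τ = 0.25 with 16 cases per condition the inflation is negligible. In the mildest ICC setting at 16 per condition, 7.1% is hard to tell from the 5% to 7% of the per-clinician test. Mixed experience implies different levels of performance, which an intercept absorbs; it makes different gains plausible but does not establish them.

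Third, the consequences are bounded. Diagnostic performance is secondary in a pilot whose primary endpoints are feasibility and usability, and the progression criterion speaks of signals rather than significance. Sensitivity and specificity are also assigned to the McNemar test, which this change leaves untouched. All of this stands and limits the weight of the point.

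Two stronger readings are tempting and not supported:

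- A reader might infer that the trial carries little more information than 36 clinician differences. The variance ratios say otherwise: at 16 per condition, 1152/1.156 = 996, 1152/1.385 = 832 and 1152/1.789 = 644 effective decisions.
- A reader might infer that the HbA1c, BMI and diabetes-duration interactions are equally affected. Those covariates vary between cases within a clinician's block, so a block effect largely cancels. Simulated at ICC 0.10, half shared, the interaction test rejected in 4.7% (16 per condition) and 4.4% (32 per condition) of null trials with common case sets, and in 8.0% and 6.8% with independently drawn cases.

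**Conclusion.** The point holds conditionally. As ordinarily read, the stated model leaves clinician-by-condition variation out of the standard error of the FibroX effect, and no other named analysis puts it back. Under the assumed ICC of 0.05 to 0.10 with 50% to 80% shared, the false-positive rate is about 7% to 14% at 16 cases per condition and about 8% to 20% at 32. It stays near 5% if FibroX helps all clinicians equally on the log-odds scale and there is no clinician-specific period shift. The direction is firm. The size cannot be pinned down, because it rests on variances the article does not report. The change is worth making before recruitment, but it concerns a secondary outcome and does not threaten the primary feasibility and usability endpoints.

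**What to change.** State the model with a provider random intercept plus a provider-by-condition random effect. In this two-period design that is equivalent to provider-by-period, so it covers both sources of variation. Base the degrees of freedom for the condition effect on the number of clinicians. If the fit is singular or does not converge, compare each clinician's difference between periods in accuracy, sensitivity or specificity between AB and BA by t test. That adjusts for period and needs no ICC. Do not revert to the intercept-only model.

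The cost is a line or two of wording, no new data, and a slightly wider interval. At 0.60 versus 0.75 the per-clinician test had 93% power against 96% for the stated model (8 cases per condition, ICC 0.05, half shared), and 99% against 99.8% (16 per condition, ICC 0.10, half shared), before allowing for case variation and dropout. The random-slope model was checked in one ICC setting and the fully shared case only, so its convergence with 36 clinicians should be tried on simulated data before the plan is locked.

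### The planned mixed model has no case-by-condition random effect, so standard errors for the FibroX effect are too small if clinicians share cases and inference goes beyond those cases

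*Protocol article*

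**What the plan says.** The Statistical Analysis section fits mixed-effects logistic regression, "specifying health care provider as a random effect and study condition, study period, and sequence assignment as fixed effects". On cases it adds: "These models will also adjust for case-level covariates such as age, BMI", and HbA1c. No random effect for case and no case-by-condition term appears. The same section says "Bootstrap resampling will be used to generate CIs for net reclassification improvement and calibration metrics", without naming the resampling unit.

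The Sample Size section states: "At least 36 health care providers (32 cases/health care provider) yield 1150 to 1280 paired decisions". It assumes "accuracy 0.60 usual care vs 0.75 FibroX" and says that the "McNemar test provides >80% power to detect a 15-point improvement at α=.05", "after accounting for health care provider–level clustering via a conservative design effect". Clustering by case is not mentioned.

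On the cases themselves, Trial Design and Oversight says that the sets used in the two periods do not overlap. Participants describes a curated library, and Interventions describes standardized cases with a FibroX risk estimate generated from each case's routine data. The library size and the rule for assigning cases to clinicians are not given.

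**The concern.** The design crosses readers with cases: a decision belongs to a clinician and to a case. For a given case FibroX shows one output. If that output is wrong, it can mislead every clinician who reads the case with the tool; if right, it can help them all. The benefit of FibroX is therefore a property of the case as well as of the clinician, and decisions on the same case are not independent pieces of information about it. Enrolling more clinicians does not reduce this source of variation; using more distinct cases does.

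Whether FibroX is right on a given case is not determined by that patient's age, BMI or HbA1c, so the planned covariates do not remove the dependence. The objective concerns adults with type 2 diabetes, not a particular set of vignettes. A provider-only model could then report an interval that is too narrow, and could declare a difference that reflects which cases were chosen. The same understatement would carry into planning the definitive trial, which the Outcomes section says these pilot estimates will inform.

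**Working it through.** **The plan's own figures.** 36 × 32 = 1152 and 40 × 32 = 1280, which match the stated range. For McNemar's test, n = (1.96√ψ + 0.842√(ψ − d²))² / d², with d = 0.75 − 0.60 = 0.15.

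- Independent pairs: ψ = 0.75 × 0.40 + 0.25 × 0.60 = 0.45, so n = 155.
- Maximum discordance: ψ = 0.40 + 0.25 = 0.65, so n = 225.

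With 1152 pairs, 80% power survives a provider design effect of up to 7.45 or 5.13. With design effect 1 + 31 × ICC, these correspond to an ICC of 0.21 or 0.13. The stated power is thus plausible on the plan's own terms. It cannot be checked exactly, because the design effect is not given.

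**Why cases limit precision: a hand check.** Suppose FibroX is right on 60% of cases, equal to the plan's usual-care accuracy, and clinicians adopt its output in half of decisions. Take 32 shared cases per period, so 64 distinct cases. The variation in which cases FibroX gets right alone adds a standard deviation of about 0.5 × √(0.60 × 0.40 / 64) = 0.031 to the estimated effect, whatever the number of clinicians. (This takes the tool's errors as unrelated to case difficulty for clinicians.) In the simulation below, the provider-only standard error in this setting is 0.020.

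**Simulation.** From the protocol: 36 clinicians, 1:1 AB/BA, two-sided α = 0.05, and 32 cases per clinician, read as 32 or as 16 per period. Assumed: clinician logit SD 0.5, case-difficulty logit SD 1, shared case sets, and no mean effect over the population of cases. Case-by-condition variation enters either as a logit SD (τ) or as the share of decisions (f) that follow a fixed per-case output. Results are for 32 cases per period, with 4000 runs of a linear analogue of the planned model. The last test column is a case-level test that lets the effect vary by case; it stands in for the crossed model.

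| Setting | Provider only | Plus case intercept | Case-by-condition allowed | True SD ÷ provider-only SE |
|---|---|---|---|---|
| τ = 0 | 3.1% | 5.1% | 4.9% | 0.91 |
| τ = 0.5 | 7.0% | 9.7% | 5.0% | 1.08 |
| τ = 1 | 17.2% | 21.9% | 5.5% | 1.44 |
| τ = 1.5 | 25.2% | 30.4% | 5.3% | 1.74 |
| f = 0.1 | 4.6% | 6.4% | 4.7% | 1.00 |
| f = 0.2 | 8.0% | 10.8% | 4.7% | 1.13 |
| f = 0.3 | 14.9% | 18.3% | 5.5% | 1.35 |
| f = 0.5 | 29.8% | 33.6% | 5.0% | 1.87 |
| f = 0.7 | 42.6% | 46.8% | 5.4% | 2.48 |

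With 16 cases per period the provider-only figures are close: 15.3%, 30.6% and 42.3% at f = 0.3, 0.5 and 0.7.

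The provider-random-intercept logistic model itself (600 runs) gave 8.8% (τ = 0.5), 20.2% (τ = 1), 31.5% (f = 0.5) and 45.2% (f = 0.7). Its τ runs carry a small non-zero mean effect (−0.003 and −0.010), which adds slightly to the first two.

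**If sets are not shared.** With each clinician drawing at random from a library, type I error was 12–18% for 200 cases and about 8% for 1000.

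**Power after correction**, at roughly the assumed 15-point effect: 99.8% and 94.2% (32 and 16 cases per period, f = 0.5), and 94.8% and 72.2% (f = 0.7).

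**The case against.** The strongest reply is that the size of the problem rests on facts that the protocol does not give. A reader might infer that all clinicians read the same 32 or 64 cases. The article gives 32 per provider and non-overlapping sets between periods, but no count of distinct cases and no assignment rule. Sharing fits standardized cases in period-specific sets, but it remains an inference. Nor do the documents support a flat statement that false positives rise several-fold: with τ of 0.5 or less, or 20% or fewer of decisions following the tool, the error rate stays below 9%.

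The simulated tool is also a simplification. FibroX gives a risk estimate and three bands, one of them indeterminate, and clinicians see the same laboratory data and may use FIB-4. If FibroX tends to fail on the cases that clinicians also find hard, case-by-condition variance is smaller. All of this stands, and it is why the result is given as a range.

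A reader might also infer that the bootstrap ignores cases. The article does not state the resampling unit, so it cannot be faulted for that choice; it need only be made explicit.

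Finally, inference limited to the cases used is defensible in a simulation pilot, and the inflation is then absent. The cases are curated, possibly synthetic and balanced across fibrosis stages, so random case effects would not by themselves license conclusions about all adults with type 2 diabetes. But the stated objective is wider than the vignettes, and the article nowhere restricts its inference to them.

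**Conclusion.** The point holds conditionally. The article commits to a model with provider as the only random effect and to a sample size that allows for provider clustering only. Given a tool whose output is fixed by the case, that omits case-by-condition variance. If cases are shared and conclusions go beyond them, standard errors for the FibroX effect are too small: by a factor of about 1.1 at τ = 0.5, and 1.35 to 2.5 when 30–70% of decisions follow the tool. The corresponding type I error is about 5–9% at the mild end and about 15–45% at the substantial end. A large library with random draws reduces the excess, and without case-by-condition variance there is none. Case difficulty alone does no harm when each shared set is read half with and half without FibroX.

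The finding does not show that the stated power is wrong: that figure is consistent with its own inputs.

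Severity is moderate. Feasibility and usability are the primary outcomes, and progression asks for signals of improved or comparable diagnostic performance, not a significant test. Yet the trial's power statement rests on accuracy, and diagnostic performance is one of the progression criteria.

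**What to change.** 1. State the number of distinct cases and how they are assigned to clinicians, periods and conditions, and report that number beside the number of decisions. Assignment matters: if one set were always read with FibroX and the other always without, case difficulty alone would give about 47% type I error in the same simulation.
2. Fit crossed random effects for clinician and case, including a case-by-condition random slope. A case intercept alone does not repair the error rate (21.9% at τ = 1, 33.6% at f = 0.5).
3. Name a multi-reader multi-case variance estimator as the prespecified fallback if the model does not converge, so that the choice does not depend on the results.
4. Base the design effect in the Sample Size section on clustering by both clinician and case.
5. State that the bootstrap resamples both clinicians and cases.

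The cost is some wording and a few lines of code, and recruitment had not begun when the article was submitted. Intervals will be wider and power somewhat lower: about 94–99.8% in three of the four scenarios checked, and 72% in the worst (16 cases per period, 70% of decisions following the tool).
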